## Abstract

**Supplementary Information:**

The online version contains supplementary material available at 10.1186/s12888-022-04464-3.

## Introduction

There are various work contexts where the workforce is predominantly male, particularly in manual, blue-collar work groups such as in construction, mining, energy and manufacturing. These are priority contexts for workplace suicide prevention for a number of reasons. Males are at higher risk of death by suicide than females: in Australia roughly three males die by suicide for every female; a pattern shared by many other developed countries [1]. Males are also less likely to seek help when distressed compared to females [2]. Hence, the gender composition of blue-collar manual occupational groups alone likely contributes to higher rates of suicide compared to other worker groups. Other evidence indicates that manual, blue-collar occupations and low educational attainment, including lower skill level within manual, blue-collar occupations (e.g., labourers versus skilled trades), are risk factors for suicide among men and young adults [3–8]. Further, particular working conditions endemic in male-dominated blue-collar industries such as construction, mining, energy and manufacturing are known to be harmful to mental health. These working conditions include long working hours, tight production timeframes, physically and psychologically demanding roles and duties, low job security, constrained autonomy, high injury rates, high prevalence of bullying, and limited mentorship and workplace support [9–12].

Protective factors for mental health and suicidality have also been documented amongst blue-collar workers. Good mentorship and patient, skilful supervision are protective factors for blue-collar workers, particularly apprentices [11, 13, 14]. Further, there is a growing evidence base that demonstrates the efficacy of the MATES in Construction workplace-based suicide prevention program for blue-collar and male-dominated industries. The MATES in Construction program was established by and for the Australian construction industry in 2007. It has also been adapted for the mining and energy sectors, and research evaluations in each sector have demonstrated the program’s positive impact on participants’ suicide prevention literacy, and willingness to seek and offer help [15–18]. However, the evidence to date has been limited to uncontrolled observational studies, with no experimental or randomised trial studies to date.

Based on a reasonable assumption that the MATES program will be relevant and likely effective in other blue-collar, male-dominated industries, the MATES program has been extended beyond the construction, mining and energy sectors, and is now being adapted for rollout in the manufacturing sector. The impetus for this suicide prevention program has come from within the manufacturing industry in the Australian state of New South Wales (NSW). Both employers and unions identified an unmet need for workers to receive support for suicidal distress, and jointly petitioned MATES in Construction to adapt its program for the manufacturing sector. MATES in Construction agreed to oversee the creation and implementation of the MATES in Manufacturing program, and to roll out the program in collaboration with a joint labour-management Steering Group in NSW.

Subsequent to the development of this initiative, funding was sought and obtained to evaluate the implementation and effectiveness of MATES in Manufacturing, hence leading to the development of this study protocol. This study will assess the implementation and effectiveness of the MATES program in the new context of manufacturing. Further, the proposed research employs a cluster-randomised controlled trial (cRCT) design, providing a much-needed complement to previously published observational evaluation evidence on MATES programs. If the results of this evaluation demonstrate the suitability and effectiveness of the MATES program in the NSW manufacturing sector, program reach could be further expanded to the broader Australian manufacturing sector and other blue-collar, male-dominated work contexts.

The following Research Questions (RQ) will be addressed using mixed methods for RQ 1–3 and quantitative methods for RQ 4–6:Was the MATES in Manufacturing program implemented as designed?What were the barriers and facilitators to participation in, and implementation of, MATES in Manufacturing?What were participant and staff experiences of the program, including any noted outcomes arising (positive, negative, or other)?Was suicide prevention literacy increased by the MATES in Manufacturing program relative to wait list controls? (process evaluation)Did intentions to seek help increase in the MATES in Manufacturing program relative to wait list controls? (primary outcome)Did help seeking behaviour increase, and levels of distress and suicidal ideation decrease, in the MATES in Manufacturing program relative to wait list controls? (secondary outcomes)

We also aim to evaluate the cost-effectiveness of the intervention if it is shown to have a significant positive effect on the primary outcome of help-seeking intentions.

## Methods

### Intervention description

MATES in Manufacturing is an adaptation of the MATES in Construction workplace suicide prevention program (https://mates.org.au/). In brief, MATES is an industry-based community development approach to workplace mental health and suicide prevention. MATES does not provide clinical services but seeks to connect distressed workers to a range of clinical and non-clinical supports, as pictorially presented in Fig. 1.

**Fig. 1 Fig1:**
[figure not shown]
Schematic representation of MATES in Manufacturing workplace suicide prevention program: General Awareness trained workers (at centre) can access or be referred to Connectors and ASIST workers on site, and on-site supports are complemented and extended by MATES case managers who can further support and refer workers in need to a range of services (illustrative examples of services in outermost ring)

Initially, a one-hour universal General Awareness Training (GAT) is provided for all workers on a site. Volunteers for half-day Living Works’ SafeTalk ‘Connector’ training are recruited during the GAT, and subsequently trained as the persons on site who can ‘connect’ workers in need to appropriate sources of help. Distressed workers can either approach a Connector him- or herself, or a Connector might approach someone based on observation, or concerns expressed by a workmate. ‘Help’ in this context is for mental health or suicidality, or for any issues that could contribute to distress, such as financial stress, alcohol and drug use, or relationship concerns. Volunteers are fundamental to the implementation of the MATES program, and the program aims to have an average of 1 in 20 workers on-site trained as Connectors. In addition to Connector training, MATES also delivers LivingWorks’ Applied Suicide Intervention Skills Training (ASIST): a 2 day session that equips participants with the skills to co-develop a safety plan with an individual at immediate risk of suicide. The program aims to have one to two ASIST-trained workers on each worksite.

Implementation of GAT on site is the starting point of the intervention. For those sites randomly assigned to intervention, the intervention will occur for 8 months during the study period, and then will continue beyond that timepoint at the discretion of the participating sites. Similarly, for sites randomly assigned to the wait-list control condition, the intervention will begin 8 months from the date of baseline assessment, and continue for at least 8 months thereafter. Participants in the trial will have indefinite access to MATES’ help line.

The MATES program is introduced to sites by Field Officers, who are employed directly by MATES. Field Officers provide GAT and ongoing support to MATES sites through regular site visits, establish and maintain relationships with workers on-site, and support site-specific Connectors in their role. In addition, MATES has a national toll-free helpline, through which workers and their immediate family members can be connected to case management support. Case managers are qualified to assist distressed workers with a plan to address their problems and concerns. This could include connecting workers with such services as their employer’s or union’s Employee Assistance Program (EAP), financial counselling, mental health services, drug and alcohol services, grief counselling, or family and relationship counselling.

The MATES in Manufacturing intervention will be delivered by the MATES in Construction NSW organisation.

### Evaluation study design

The MATES in Manufacturing intervention will be evaluated using a mixed methods implementation evaluation combined with a two-arm cluster-randomised trial design with wait-list controls for effectiveness evaluation. Implementation will be evaluated quantitatively by monitoring numbers and types of intervention activities and associated participation rates as well as suicide prevention literacy as a process evaluation measure. Qualitative implementation evaluation will entail characterising barriers and facilitators to implementation as well as participant experiences. Following SPIRIT Guidelines, the cRCT evaluation will assess help-seeking intentions as the primary outcomes, and help sought, suicidality, and psychological distress as secondary outcomes (see SPIRT Checklist, Supplementary File 1).

### Study setting & participants

The research project setting will be manufacturing worksites in the eastern Australia state of NSW that participate in the MATES in Manufacturing program.

#### Recruitment of participants within study sites (clusters)

All workers employed at each participating site will be eligible for the MATES program and all will be invited to participate in baseline and follow-up surveys (census sampling). We expect participants to be disproportionately male and blue-collar workers (estimated 75% males in Australian manufacturing sector). There will be two i*nclusion criteria: 1)* Employees or workers in the manufacturing industry who are working at participating sites of the MATES in Manufacturing program, including casual/temporary, contract, and continuing/permanent employees, and 2) Basic English proficiency for program activities (which will be conducted in English); however, surveys and some printed information on the program have also been translated into Vietnamese and Mandarin, and are available on an as-needed basis (some sites include a number of Vietnamese and Chinese workers). There is one e*xclusion criterion:* Individuals aged under 18 years.

### Sequence generation, randomisation and allocation concealment

Allocation of sites (clusters) to intervention arms will be conducted by the project statistician (AM) using minimisation implemented with the *rct_minim* procedure in Stata. Balance will be sought for a single factor – site size – with sites of less than 150 workers classified as ‘small’ and sites of 150 or more workers classed as ‘large.’ Due to resource limitations, participating sites will be randomly assigned to intervention or wait-list control in small batches of up to four sites (further detail below). Allocations will then be revealed to the research team, MATES field staff and sites, as blinding beyond the baseline assessments will not be feasible.

### Data collection (1): quantitative effectiveness evaluation

MATES will be the direct contact for recruitment, intervention, and data collection. All data will be collected by MATES Field Officers and research staff directly from workers, with no survey responses or data being shared with companies/employers. MATES Field Officers have access to and have been trained to adhere to a structured data collection protocol. All are experienced with data collection and have administered surveys as part of previous evaluation research projects.

Data collection will occur at each worksite, within work hours, at a date and time agreed with the company / site managers. Field Officers will deliver a brief preamble about the study purpose and aims. Workers will be informed that survey data collection and participation in MATES in Manufacturing as a program are separate processes: workers are welcome to participate in the program but are not compelled to participate in the surveys. There is no penalty for not completing a survey.

Workers will be given a plain language statement, consent form, and survey form to peruse, and the consent process will be explained verbally. Interested workers will be asked to sign the consent form to confirm their willingness to participate, and Field Officers will answer any questions arising. Participants will be invited to seal their consent form and survey in a provided envelope (with or without responses) and place it into a data collection box. This will help ensure that those who do not wish to participate in surveys will not be readily identifiable. See Supplementary File 2 for Plain Language Statements and Consent Forms.

At the end of the site visit, the data collection box will be removed from the site by MATES Field Staff. This box will then be transported, by courier, to the MATES Research Manager who is based in the Queensland office, where it will be entered into a secure electronic database. Survey responses will not be handled by or made available to employers.

Data for the economic evaluation will be collected as a supplementary survey at time 2 (8 months) for both intervention and wait-list control sites. Following administration of the paper ‘core’ survey, participants will be invited to scan a QR code and complete a brief health service use questionnaire.

#### Data collection safety measures

Because respondents will be asked sensitive questions (e.g., about suicide), we prepared a safety protocol for data collection and intervention activities. We have three mechanisms in place for following up with participants who indicate (either verbally or through physical non-verbal cues) that they are upset or in distress at the time of data collection or during program activities, and for following up with participants who indicate through their survey responses that they have recently experienced psychological distress:Field Officers will observe participants throughout survey administration. Anyone who appears to be uncomfortable or upset will be offered immediate support. All Field Officers have completed Applied Suicide Intervention Skills Training, and all are experienced with supporting individuals in distress;At the end of their survey (tick box question on survey) or by direct in-person request, participants will be able to indicate that they would like a follow-up support call from MATES. This is a mechanism that all MATES programs use during training and in survey administration for other program evaluation projects (participants can self-nominate whether they would like a follow up call after training sessions). All requests for follow up calls will be addressed immediately;As soon as surveys are returned, the Research Manager will review responses for any indications that a participant is in distress, or has recently been in distress (e. g., ‘rather likely’ or ‘very likely’ responses to the question “How likely is it that you will attempt suicide someday?”). This too will trigger immediate follow up via phone, and referral to MATES case management staff.

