#### Suicidal behaviour (secondary outcome)

Suicidal behaviour will be measured using 2-items from the 4-item version of the Suicidal Behaviour Questionnaire-Revised (SBQ-R) [21]. The first item assesses the frequency of suicidal ideation in the past 6 months, and responses will be dichotomised (never/ever). The second item measures the likelihood of suicidal behaviour in the future (no chance/unlikely/likely).

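### Support-call requests ticked on the paper survey cannot be addressed immediately under the sealed-envelope and courier route that the protocol describes

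*Protocol article*

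**What the plan says.** Under Data collection safety measures, the protocol article lists three mechanisms for distressed participants.

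- Field Officers observe participants during the survey and offer support on the spot.
- Participants can ask for a support call, either in person or by a tick box at the end of the survey. Of these requests the article says: "All requests for follow up calls will be addressed immediately".
- Survey answers are read for signs of distress: "As soon as surveys are returned, the Research Manager will review responses". A flagged answer then leads to an immediate phone call and referral to case management. The example given is "rather likely’ or ‘very likely’ responses to the question" "How likely is it that you will attempt suicide someday".

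Under Data collection (1), participants are invited to seal the consent form and survey in an envelope and put it in a collection box. Field staff remove the box at the end of the visit. Then: "This box will then be transported, by courier, to the MATES Research Manager who is based in the Queensland office". Under Study setting & participants, the sites are in New South Wales, so this leg crosses a state border. No transit time is given.

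Under Suicidal behaviour (secondary outcome), two items are described. For the first, on past ideation, "responses will be dichotomised (never/ever"). For the other: "The second item measures the likelihood of suicidal behaviour in the future (no chance/unlikely/likely").

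**The concern.** The tick box is a route for a worker who wants help but shows no visible sign and would rather not ask aloud in front of colleagues. If the worker is led to expect a prompt call and the form is in transit, the worker waits without knowing it and may not use a faster channel. The protocol thus states a safety property that its own data flow does not provide.

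The response labels raise a smaller question. The only concrete example of an answer that prompts follow-up uses two labels that do not appear where the item is described as an outcome. A reader cannot tell which options are printed on the form, or how they are grouped for analysis.

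**Working it through.** No arithmetic bears on this point, so the check sets the sections side by side.

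**Tick-box requests**

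1. The tick box is on the survey itself (Data collection safety measures).
2. The survey goes into an envelope that the participant is invited to seal, then into a box. The stated purpose is that those who do not wish to take part cannot readily be identified (Data collection (1)).
3. The box leaves the site only when the visit ends, and goes by courier to the Research Manager. No step before that has anyone opening an envelope or looking for ticked boxes.
4. The name and mobile number needed to make a call are collected with the survey data (Covariates), so the described route makes them available only once the form is opened.
5. The promise on call requests covers all of them and carries no condition that the form has first been returned.

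Steps 1 to 4 give a wait equal to the rest of the visit, plus courier transit, plus the time to open and read the forms. Step 5 promises no wait. For paper requests both cannot hold. In-person requests are unaffected.

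**Flagged answers**

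Here the review starts on return of the surveys, and the phone call is immediate once the review flags an answer. Both sections can be true together. What remains is that the time from completing the form to the review is not stated and has no upper limit.

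**Response labels**

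| Section | Labels for likelihood of future suicidal behaviour |
|---|---|
| Data collection safety measures | rather likely, very likely (as examples) |
| Suicidal behaviour (secondary outcome) | no chance, unlikely, likely |

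Two readings are possible.

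- If the second row shows the printed options, the example in the first row cannot occur as worded.
- If the second row shows collapsed analysis categories, the example may be correct, but the collapsing is unstated. For the companion item the article says outright that responses are dichotomised. For this item it says nothing about recoding.

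The survey form is not shown, so the documents do not settle which reading is right.

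**The case against.** The strongest reply is that this is an article, and that it says a safety protocol was prepared, which is not shown. That document could provide for opening envelopes on site, or could define the promise as running from receipt. Other channels also do not depend on the courier: on-site observation, direct requests to a Field Officer, and the toll-free helpline, to which trial participants have indefinite access (Intervention description). The article reports under Trial status that distressed workers were identified and followed up during piloting and at baseline in both arms, and that they were few.

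Much of this stands. It rules out calling the paper survey the only way to reach a distressed worker. It does not remove the conflict, because the article itself states both the unconditional promise and the route that prevents it.

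A reader might go further and infer that a worker reporting a likely attempt could be missed because the label *likely* is not a named trigger. The documents do not support that. The named options are introduced as examples, and "the Research Manager will review responses for any indications that a participant is in distress", now or recently. An answer of *likely* falls plainly within that review.

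A reader might also infer that the immediate follow-up of flagged answers contradicts the courier route. It does not, because that review is tied to return of the surveys.

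Nor does the number of forms measure harm. Average participation of 74% applied to 1573 workers gives 0.74 × 1573 ≈ 1,164 baseline forms at the first 8 sites. That counts everyone who used this route, not those who asked for a call or gave a worrying answer.

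**Conclusion.** The point holds for call requests made by tick box on the paper survey: as described, they cannot be addressed immediately. For flagged answers there is no contradiction, only a delay of unstated length between completion and review. The label mismatch is a secondary matter of clarity.

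The size cannot be put in days from the documents. If courier transit took 1 to 3 days, which is purely an assumption, each paper request would wait at least that long. The conclusion does not depend on that range, since any interstate transit is incompatible with an unconditional promise of immediate action.

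The conclusion assumes that nobody opens the envelopes before they reach Queensland, which is how the article reads. If an unshown procedure provides otherwise, the article should say so. The point still matters in practice: when the article was submitted, a third group of sites had yet to complete baseline surveys, and 8-month surveys are planned at every site.

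**What to change.** 1. Reconcile Data collection (1) with Data collection safety measures. Either bring the handling of tick-box requests into line with the stated promise, or replace the promise with the interval from survey completion that the courier route delivers. State the interval for flagged answers as well. Which interval is acceptable is for the clinical team.
2. If the interval is restated, tell participants at survey administration, so that they know an in-person request or the helpline is the faster route. The plain language statements (Supplementary File 2) are not shown and may already say this; if so, the article should match them.
3. State whether the three levels under Suicidal behaviour are the printed options or collapsed categories. If collapsed, give the recoding. Express the example trigger in the printed options, with the cut left to the clinical team.

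Restating the interval and clarifying the labels costs protocol wording, a sentence in the Field Officers' preamble and possibly an ethics notification. Changing the route costs more. It would probably mean opening forms on site or moving the review closer, and would have to be weighed against the confidentiality that the sealed envelopes protect. Neither course needs new outcome data.
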